### 9.2 Secondary study parameter(s)

The generated data will be analyzed through SPSS (version 29). Baseline demographic, medical characteristics and secondary outcome measures of the included patients will be summarized. *If the* results are normally distributed, results will be reported as mean (standard deviation). If there is a non-normal distribution, results will be reported as median (interquartile ranges) or number (percentage). Several sensitivity analyses are being anticipated. Several subgroup analyses are investigated (e.g. PE, FGR, PPRM).

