### 4.2 Inclusion criteria

In order to be eligible to participate in this study, a subject must meet all of the following criteria:

- Minimum age of 18 years old
- Pregnant patients with a gestational age between 32+0 and 36+6 weeks and days
- Singleton pregnancy
- Any indication for fetal monitoring at least twice per week (e.g.):
  - PE
  - FGR
  - PPRM
- Absence of exclusion criteria > 24 hours after admission.
- Oral and written informed consent is obtained.

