### 5.1 Investigational treatment

All patients will receive routine care following national guidelines and/or local protocols. Participants at the clinic will receive self-administered remote eCTG monitoring by NRM once a day (*Figure 1*). In case of follow-up at the outpatient clinic, participants will receive self-administered remote eCTG monitoring by NRM once per day or at least twice a week, depending on their care path. The realtime eCTG measurement will be instantly transferred digitally to the hospital electronic patient file (Chipsoft HiX) and assessed real-time on interpretability by the HCP. Monitoring will last between 30-90 minutes depending on the interpretability and reassurance of the remote eCTG measurement. Criteria defining a successful measurement are described in a standard operating procedure (SOP) and will be available for HCPs at the hospital to avoid prematurely closing of the eCTG measurement (see section 7.1.1). All HCPs involved in this study will receive training on the study protocol. The study procedure and statistical analysis are described in section 7.3.2, chapter 9 and in *Figure 12*.

Monitoring will be repeated the same day when reassuring but insufficiently interpretable, or upon request of the HCP in case of concerns about maternal and/or fetal condition. Additional detailed information of the NRM is described under investigational product (chapter 6). When remote eCTG interpretability is insufficient – based on clinical assessment of HCPs – a switch to conventional CTG monitoring will take place. In this study, HCPs will be asked to define clearly if a switch to conventional CTG was made based on insufficient interpretability or because of concerns about fetal and/or maternal condition (section 7.1.2).

From the second day onward, synchronized US Doppler measurements (clips of 2 x 5 minutes) of the umbilical and uterine arteries will be performed simultaneously with the remote eCTG for 24 patients ([images removed]

*Figure 3*). Measurements of two groups - cardiovascular low (PPROM; N=12) versus cardiovascular high-risk (PE/FGR; N=12) - will be collected and analyzed to evaluate the feasibility of synchronized multimodal acquisitions of maternal and fetal measurements.

[images removed]

*Figure 3. Measurement fetal and maternal heartrate, Doppler arteria umbilicalis, Doppler uterine artery and uterine activity.*

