#### 7.1.2 Secondary study parameters

##### *Remote eCTG parameters*

- Number of days with remote monitoring per participant.
- Number of remote eCTG measurements per participant.
- Need to repeat remote measurements the same day because of reassuring but insufficient interpretability.
- Number of switch to conventional CTG and possible maternal and/or fetal reason.
- Number of switch to conventional CTG needed because of poor signal of remote eCTG measurement and possible cause.
- Success rate of CTG measurement after switch based on same criteria as in remote eCTG monitoring (7.1.1).
- Incidence of skin irritation.
- Number of “unscheduled visits” and reason.
  - When there is an indication for an additional visit in-hospital as if the participant is monitored at home (e.g. contractions, decreased fetal movements, PE symptoms, suspicion of PPRM).
- Number of “re-admissions” and reason.
  - When there is an indication of admission as if the participant is monitored at home (e.g. blood loss, threatened premature labor, hypertension with indication for intravenous medication).
- The number of eCTG measurements assessed successful at closure by HCP.
- The number of eCTG measurements prematurely closed by HCP before complying the criteria of a successful measurement (7.1.1).

- Maternal and fetal factors HCPs have included in their assessment of the eCTG measurement (e.g. GA, fetal growth, Doppler measurements, PPRM).

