- Once the eCTG measurement is considered successful – or when the maximum of 90 minutes has exceeded – the HCP will send a message in the Luscii app® and will contact the participant by telephone a few minutes later, the time they have stopped the remote eCTG measurement. All findings will be discussed with the participant and completed in the patients' file in HiX. In addition, the HCP will visit the participant in the hospital room.
- When eCTG measurement is not successful but reassuring, the measurement will be repeated the same day on a moment agreed between participant and HCP (PA).
- When eCTG measurement is not interpretable after repetition on the first day of inclusion, eCTG will be defined not successful – primary outcome – and a switch to conventional CTG will take place. Equally to routine care, in- hospital care is needed and home- monitoring will not be possible.
- When after an additional clinical visit by the HCP (PA) “unscheduled consult” at participants room for other reasons than signal quality concerns (e.g. contractions, reduced fetal movements, patients concerns), without indication for hospitalization – eCTG adequate and reassuring – participants can continue “home monitoring” through eCTG like it will be once home monitoring is implemented in the future. No switch to conventional CTG will be needed. This additional visit will be recorded as part of the patient journey for later cost analysis purposes (*Figure 11, Table 2*).
- As long as remote eCTG measurements are successful, participants will continue the study interventions until discharge, delivery or when 37 weeks is reached. At any moment – when demanded by the participants or by the HCP – a switch to conventional CTG will be made.
- When reached a GA of 37 weeks, after delivery or at discharge, participants will be asked to fill in a second digital questionnaire (5.1, 7.3.3), and at 4 weeks after delivery a third questionnaire.

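### Section 9.2 gives secondary event counts no exposure denominator, although time on eCTG runs by design from 1 to 35 days and recording frequency differs by care path

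*Protocol*

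**What the plan says.** Section 9.2 covers all secondary outcomes with one rule. They are summarised for the included patients as mean (SD) when normally distributed, and otherwise: "If there is a non-normal distribution, results will be reported as median (interquartile ranges) or number (percentage"). The section also announces subgroup analyses by diagnosis (PE, FGR, PPROM). It mentions no rate, person-time or per-recording denominator.

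Among the remote eCTG parameters, section 7.1.2 lists same-day repeats, switches to conventional CTG, unscheduled visits and re-admissions. One entry reads "Number of switch to conventional CTG needed because of poor signal of remote eCTG measurement and possible cause". The visits and re-admissions are those that would have been needed had the woman been at home. The same list includes two measures of exposure: "Number of days with remote monitoring per participant", and the number of remote eCTG measurements per participant.

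Exposure is set elsewhere:

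- Entry (section 4.2): "Pregnant patients with a gestational age between 32+0 and 36+6 weeks and days".
- End (section 7.3.2): while measurements succeed, "participants will continue the study interventions until discharge, delivery or when 37 weeks is reached".
- Frequency (section 5.1): for women at the clinic (the ward group), "Participants at the clinic will receive self-administered remote eCTG monitoring by NRM once a day". For women followed at the outpatient clinic, "once per day or at least twice a week, depending on their care path".
- Early exit (section 7.3.2, both care paths): if the repeated eCTG on the first day is still not interpretable, the woman is switched to conventional CTG and home monitoring is no longer possible for her.

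**The concern.** These events show how often home monitoring would have broken down, which is a central practical question in a feasibility study. A woman monitored for a month has many more opportunities for an unscheduled visit or a repeated recording than a woman monitored for two days. A mean count per woman, or a percentage of women with at least one event, combines the underlying rate with the length of monitoring.

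This matters in two places. First, the diagnosis subgroups in 9.2 and the ward versus outpatient split may differ in days monitored or recordings made, and crude counts would then differ even at equal rates. Second, a count without a denominator cannot be carried over to a future home programme with a different duration. In addition, women who fail on the first day cannot later have an as-if-at-home visit or re-admission, but they remain included patients.

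**Working it through.** The protocol states neither an exposure range nor an event rate, so there is no figure to reproduce. The check derives the exposure range from the entry and stopping rules, then shows what exposure alone does to the summaries.

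**1. Days.** 32+0 is day 32 × 7 = 224; 36+6 is day 36 × 7 + 6 = 258; 37+0 is day 37 × 7 = 259.
- Longest: 259 − 224 = 35 days.
- Shortest when monitored to 37 weeks: 259 − 258 = 1 day.
- Discharge or delivery can shorten any stay.

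**2. Recordings over 35 days (5 weeks), not counting repeats.**
- Daily: 35.
- Twice weekly: 2 × 5 = 10.
- Ratio: 35 / 10 = 3.5.

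**3. Effect at equal risk (illustration).** Section 4.4 cites a first-trace success rate of 95.5% in a cohort of conventional remote CTG, which gives r = 1 − 0.955 = 0.045 per recording. It is used here only as a constant, independent risk. With m recordings, the expected count is r·m and P(at least one) = 1 − (1 − r)^m.

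| Recordings m | Expected repeats per woman | At least one repeat | Repeats per 100 recordings |
|---|---|---|---|
| 1 | 0.045 | 4.5% | 4.5 |
| 10 | 0.45 | 36.9% | 4.5 |
| 35 | 1.58 | 80.0% | 4.5 |

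The per-woman summaries change with m; the per-recording rate does not.

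**4. How much of the spread between women could exposure explain?** If counts are Poisson given exposure, the share of variance due to exposure is r²·Var(m) / [r²·Var(m) + r·E(m)]. Assumption: days uniform on 1 to 35.
- All daily: E(m) = 18, Var(m) = (35² − 1)/12 = 102. At r = 0.05: 0.0025 × 102 = 0.255 and 0.05 × 18 = 0.90, so 0.255/1.155 = 22%. At r = 0.02 and 0.10 the shares are 10% and 36%.
- Half daily, half twice weekly (recordings = 2 × days/7, rounded, at least 1): E(m) = 11.59, Var(m) = 96.2. The shares are 14%, 29% and 45% at r = 0.02, 0.05 and 0.10.

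Exposure is thus a material part of the spread, but below half in every scenario.

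**5. First-day failures.** At the 90% success rate assumed in section 4.4, 60 × 0.10 = 6 women leave home monitoring on the first day. If they count as zeros for later visits and re-admissions, the mean over 60 is 54/60 = 0.90 of the mean over the 54 who continue. That is a reduction of up to 10%.

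**The case against.** The strongest reply is that 9.2 is a general formatting rule and does not prescribe counts per woman for these outcomes. For repeats and switches this stands. In 7.1.2 only days and number of measurements are worded per participant, neighbouring items count measurements, and the benchmark in 4.4 is per tracing (562 of 12,649). Number (percentage) could therefore already mean of recordings. For unscheduled visits and re-admissions the reply is weaker. Section 9.2 refers to the included patients, a recording is not a natural unit for a visit, and the cost section of 7.1.2 takes unscheduled visits per patient.

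It can also be said that a denominator is a detail for a statistical analysis plan. Both quantities are collected and nothing rules out a rate. But 9.2 does state a summary method, and that method does not suit these outcomes when exposure varies this much by design.

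Three further points stand:
- Per-woman totals are a legitimate quantity. The patient-journey cost analysis needs them, and it already plans sub-analyses for ward and outpatient paths.
- Switches do not simply accumulate with time. A first-day switch ends exposure and is not caused by long exposure.
- It is an inference that first-day failures enter as zeros for visits and re-admissions; the protocol does not say so. For repeats and switches these women contribute events.

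A reader might go further and infer that the counts mainly reflect exposure, or that identical device performance could put the cohort's percentage anywhere from 4.5% to 80%. The documents support neither. The calculated shares stay below one half, and the extremes would need every woman to have 1 recording or every woman to have 35. Section 7.3.1 says delivery can occur within a few days, so 35 days is a design limit and not a typical stay. Unscheduled visits also arise from contractions, fetal movements or symptoms, and so do not measure device performance alone.

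**Conclusion.** The concern holds in limited form. With no exposure denominator in 9.2, crude per-woman counts of unscheduled visits and re-admissions, and of repeats and switches if counted per woman, are partly confounded by time on eCTG. They are not comparable between care paths or between the PE, FGR and PPROM subgroups.

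The ranges of 1 to 35 days and 10 to 35 recordings follow from the protocol's own rules. The 4.5% risk is borrowed from conventional CTG. The variance shares of about 10% to 45% rest on assumed uniform exposure and assumed risks of 2% to 10%. The true size is unknown, because the protocol gives no exposure distribution.

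These outcomes are secondary and descriptive, in a single cohort with no stated test or decision rule on them. The primary endpoint uses only the first day and is unaffected. This is a cheap improvement and not a threat to the main result.

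**What to change.** Add to section 9.2:

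- Report unscheduled visits and re-admissions per 100 days with remote monitoring. State whether this means calendar days under monitoring or only days with a recording, because the two differ for women recorded twice a week.
- Report same-day repeats and poor-signal switches per 100 eCTG recordings.
- Give 95% confidence intervals that treat the woman as the cluster, overall and by care path (ward, outpatient clinic). Use the same rates in any diagnosis subgroup.
- Show first-day switches separately, because they end exposure.
- Keep the per-woman totals alongside, because the cost analysis needs them.

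The cost is a few sentences and minor extra programming. Intervals will be wide in small subgroups. No new data are needed, since days and recordings per participant are already secondary parameters in 7.1.2. Fixing the denominators now also prevents them from being chosen after the data are seen.

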#### 9.2.1 The questionnaire data

The questionnaires will be analyzed and will be summarized. The EQ-5D-5L questionnaire - including EQ VAS - 4 weeks after delivery will not be compared to the results at inclusion since no direct causality is expected. Where possible, the results of the EQ-5D-5L, EQ VAS and CSQ-8 questionnaires – where possible – will be descriptively compared to the outcomes of the HoTeL study (10).

- EQ-5D-5L (36): Questionnaire assessing wellbeing. Summary statistics will be derived, including numbers of patients and proportions of categorical responses for the five EQ-5D dimensions. Results will be reported as mean (SD), minimum, median and maximum will be provided for change from inclusion to 4 weeks after delivery.
- EQ VAS (Visual Analogue Scale) - score between 0 and 100 - will be summarized. Results will be reported as mean (SD), minimum, median and maximum will be provided for change from inclusion to 4 weeks after delivery.
- D-QUEST (35): Questionnaire of 12 aspects that can influence the users' satisfaction of a device and the provision process. Results will be reported as not satisfied at all, displeased, more or less satisfied, satisfied or very satisfied.
- CSQ-8 (31): Client/patient Satisfaction Questionnaire of 8 items including scores from 1 to 4. Items 2, 4, 5, and 8 are reverse scored. Total scores range from 8 to 32, with the higher number indicating greater satisfaction. Results will be reported as mean (SD), minimum and maximum.

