#### **2. Did you get the kind of service you wanted?**

- No, definitely not (1)
- No, not really (2)
- Yes, generally (3)
- Yes, definitely (4)

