#### **5. How satisfied are you with the amount of help you received?**

- Quite dissatisfied (1)
- Indifferent or mildly dissatisfied (2)
- Mostly satisfied (3)
- Very satisfied (4)

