**Scoring:**

Scores are summed across items once.

Items 2, 4, 5, and 8 are reverse scored.

Total scores range from 8 to 32, with the higher number indicating greater satisfaction.

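### The CSQ-8 rule to reverse items 2, 4, 5 and 8 conflicts with the codes printed in Appendix C, which already run from 1 (least) to 4 (most satisfied) on all eight items

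*Protocol*

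**What the plan says.** Section 9.2.1 describes the CSQ-8 as a "Client/patient Satisfaction Questionnaire of 8 items including scores from 1 to 4". It then gives the rule "Items 2, 4, 5, and 8 are reverse scored" and the property "Total scores range from 8 to 32, with the higher number indicating greater satisfaction". Results are to be reported as mean (SD), minimum and maximum and, where possible, compared descriptively with the earlier randomised home-telemonitoring trial (HoTeL).

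The scoring block at the end of Appendix C says "Scores are summed across items once" and repeats the reversal rule and the range.

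The items in Appendix C carry printed codes. Item 2 runs from "No, definitely not (1") to "Yes, definitely (4"). Items 4 and 8 have the same end points. Item 5 runs from "Quite dissatisfied (1") to "Very satisfied (4"). Items 1, 3, 6 and 7 list the best answer first and also give it the code 4.

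**The concern.** Reverse scoring is needed when some items are coded in the opposite direction to the rest. Here none are. Items 2, 4, 5 and 8 differ from the others only in listing the worst answer first, and their printed codes already allow for that. An analyst who follows the written rule would recode four items that need no recoding.

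Patient satisfaction is a named secondary objective (section 2.2), and the CSQ-8, completed four weeks after delivery, is one of its instruments (section 7.1.2). If the rule is carried out on the printed codes, the reported mean and SD no longer describe satisfaction, and the comparison with HoTeL sets two different quantities side by side. The error would be easy to miss. Every wrongly scored total still lies between 8 and 32, so a range check passes, and a mean near 20 could be taken for middling satisfaction.

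**Working it through.** **Inputs, all from Appendix C and section 9.2.1**

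| Items | Order of answers | Code of worst answer | Code of best answer | Stated rule |
|---|---|---|---|---|
| 1, 3, 6, 7 | best first | 1 | 4 | use as is |
| 2, 4, 5, 8 | worst first | 1 | 4 | reverse |

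Stated total: 8 to 32, with higher meaning more satisfied.

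**Step 1. Reproduce the stated range and direction.** Sum the printed codes without reversal. All worst answers give 8 × 1 = 8, and all best answers give 8 × 4 = 32. Uniform answers of 2 and 3 give 16 and 24. This is the stated range in the stated direction.

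**Step 2. Apply the written rule to the printed codes.** Reversing a 1–4 code x gives 5 − x. With A = items 1+3+6+7 and B = items 2+4+5+8:

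Total = A + (4 × 5 − B) = 20 + A − B

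| Every item answered | A | B | Sum of printed codes | Total under the rule |
|---|---|---|---|---|
| 1 | 4 | 4 | 8 | 20 + 4 − 4 = 20 |
| 2 | 8 | 8 | 16 | 20 + 8 − 8 = 20 |
| 3 | 12 | 12 | 24 | 20 + 12 − 12 = 20 |
| 4 | 16 | 16 | 32 | 20 + 16 − 16 = 20 |

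**Step 3. What the total then measures.** It varies only with A − B.

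- A total of 32 needs A = 16 and B = 4: best answers on four items and worst on the other four. The plain sum of that pattern is 16 + 4 = 20.
- A total of 8 needs the opposite pattern, A = 4 and B = 16.
- Take a woman who gives the best answer everywhere except a 3 on item 2. Her total is 20 + 16 − 15 = 21, above the 20 of a woman who is satisfied on every item. If the single 3 is on item 1 instead, the total is 20 + 15 − 16 = 19. Being less satisfied on a reversed item raises the score.

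**Step 4. Would the rule be right if the form stored the position of the answer?** Number the answers 1 to 4 in printed order. The best answer is then position 1 on items 1, 3, 6 and 7 and position 4 on items 2, 4, 5 and 8. Reversing 2, 4, 5 and 8 gives:

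- fully satisfied: 4 × 1 + 4 × (5 − 4) = 8
- fully dissatisfied: 4 × 4 + 4 × (5 − 1) = 32

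The scale is inverted. Under position coding it is items 1, 3, 6 and 7 that would need reversal: fully satisfied is then 4 × (5 − 1) + 4 × 4 = 32. The rule therefore fails under either coding of this form.

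**The case against.** The strongest reply is that the sentence only describes the form. On this view, items 2, 4, 5 and 8 are those whose answers run in the opposite order and whose printed codes already take care of it. These are exactly the four items named, and summing the printed codes satisfies everything else in the two passages. It is the only reading under which the text is consistent, and it may be what was intended. But neither place says so. One sentence stands in the statistical analysis chapter and the other in a block about scoring, and both read as instructions.

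Three further points limit the concern, and they stand.

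- The CSQ-8 total is descriptive, has no hypothesis test, and is one of several satisfaction measures in a single-arm study of 60 women.
- If item answers are kept, a wrong total can be recalculated without new data.
- The comparison with HoTeL is planned only where possible, and it is spoiled only if the rule is actually applied as written.

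A reader might infer that the total would carry no information on satisfaction at all. The documents do not support that. A constant 20 is exact only when the two halves have equal sums. Otherwise the total still varies, but with the difference between the halves and not with the overall level. How far the halves differ in these women cannot be known from the protocol. A reader might also infer that the outcome is certain to be lost. That does not follow either, because the protocol does not show how the database codes or scores the answers.

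**Conclusion.** The rule is wrong as written for the form in Appendix C. Applied to the printed codes it gives 20 + A − B, scores every uniform responder at 20, and contradicts the direction that the same paragraph states. The arithmetic is exact. It assumes only that reversal means 5 minus the code, which is the usual meaning on a 1–4 scale, and that the printed codes are the ones stored.

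The effect is confined to one secondary descriptive outcome: its mean, SD, minimum and maximum, and the descriptive comparison with HoTeL. The primary endpoint and the sample size do not depend on it. It should be fixed before the CSQ-8 is scored, but it does not threaten the study's main conclusion.

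**What to change.** Delete the reversal sentence in section 9.2.1 and in the Appendix C scoring block. Replace it in both places with: *Sum the printed codes of the eight items (1–4, 4 = most satisfied); no further reversal.*

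Confirm that Research Manager exports the printed codes and not the position of the answer, and keep the item-level answers so that totals can be rescored. Limiting the existing rule to answer position would not repair it, since step 4 of the working shows that this inverts the scale.

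The cost is one sentence in two places and one check of the export. No new data are needed.
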